**Primary objective**				
To evaluate to what extent SO is acceptable, to survivors and wider stakeholders	Acceptability of intervention Measure Semi-structured interviews (to explore reasons for acceptability score)	Quantitative Qualitative	T1, T2, T3 T2, T3	Stroke survivors, deliverers, supporters, referrers Stroke survivors, deliverers, supporters, referrers
**Secondary objectives**				
To evaluate to what extent SO are appropriate to survivors and wider stakeholders	Intervention Appropriateness Measure Semi-structured interviews (to explore reasons for appropriateness score)	Quantitative Qualitative	T1, T2, T3 T2, T3	Stroke survivors, deliverers, supporters, referrers Stroke survivors, deliverers, supporters, referrers
To evaluate to what extent Stroke Odysseys feasible to survivors and wider stakeholders	Feasibility Intervention Measure Semi-structured interviews (to explore reasons for feasibility score)	Quantitative Qualitative	T1, T2, T3 T2, T3	Stroke survivors, deliverers, supporters, referrers Stroke survivors, deliverers, supporters, referrers
To assess any unintended consequences of the programme	Semi-structured interviews	Qualitative	T2, T3	Stroke survivors, deliverers, supporters, referrers
To explore the facilitators and barriers to implementing the programme	Semi-structured interviews	Qualitative	T2, T3	Stroke survivors, deliverers, supporters, referrers
To explore the facilitators and barriers to sustained use of the programme	Semi-structured interviews	Qualitative	T2, T3	Stroke survivors, deliverers, supporters, referrers
To assess service utilisation and cost associated costs and changes in quality of life associated with the implementation of the programme	EQ5D-5L (quality of life measure) and AD-SUS (adult service receipt schedule) and semi-structured interviews and activity data (to estimate implementation costs).	Quantitative	T2 and T3	Stroke survivors Stroke survivors, deliverers, supporters, referrers
To explore the strategies including resource inputs used, used within individual sites to implement the programme	Semi-structured interviews	Qualitative	T2, T3	Deliverers, referrers
To assess the adoption of the programme	The number of individuals delivering the programme, and the number of individuals supporting the programme (and continuing to do so)	Quantitative	T0, T2, T3	Deliverers, referrers
To assess programme adherence and attrition rates	Data on the overall adherence to the programme, number of drops-outs and reasons why	Quantitative Qualitative	Data recorded from the register on weekly attendance rates for the 12 week programme (stage 1) and 4 week ambassador programme (stage 2) T2, T3	Deliverers (record data) Stroke survivors

Data on the implementation outcomes will be collected from stroke survivors who have enrolled on the SO programme as well as the wider stakeholder group involved in the SO programme (including deliverers, referrers and supports).

^1^ Adult Service Use Schedule (AD-SUS)

SO, Stroke Odysseys.

Demographic data will be collected by Rosetta Life at the time of enrolment.

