### Outcomes

Data on the clinical outcomes will be collected from stroke survivors who have enrolled on the SO programme (see table 1). Data on the implementation outcomes will be collected from stroke survivors who have enrolled on the SO programme as well as the wider stakeholder group involved in the SO programme, including deliverers, referrers and supporters (see table 2).

Time points for data collection: T0—baseline; T1—midway through the 12-week programme (weeks 5–7); T2—immediately postperformance (12–14 weeks); T3—immediately after the advocacy training for stroke ambassadors.

To maximise inclusivity and outcome completion, and minimise participant burden, outcome assessments, where possible, will be conducted either face-to-face, online, by telephone or via postal questionnaire depending on the outcome measures being assessed, participants’ preferences and government COVID-19 guidelines.

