### Assessment descriptions for the implementation outcomes

#### Quantitative assessments

Validated and standardised implementation scales will be used to gather quantitative data on how acceptable, appropriate and feasible the SO programme is perceived by stroke survivors, ambassadors, deliverers, supporters and referrers. These scales include the Acceptability of Programme Measure (AIM), the Programme Appropriateness Measure (IAM) and the Feasibility of Programme Measure (FIM). For further information on the development of these scales, please refer to the paper by Weiner *et al*.^24^

The implementation science researchers will quantify and cost the resources used in implementing the programme, evaluate wider service utilisation and associated costs before and after participants complete the programme, including any changes to their quality-of-life profile measured using the EQ5D-3L preference-based QoL measure. The EQ5D-3L is a self-complete multiattribute measure of health-related quality of life that assigns individuals a unique state of health based on their response to individual items. Each unique health state is associated with a predetermined ‘utility’ value derived from a survey of wider community preferences over different states of health. The utility scale is anchored at 1 (full health) and zero (death), with negative values allowed in instances where states of health are considered worse than death. Health state utility values are subsequently used to estimate quality-adjusted life years (QALYs) survived over time—the utility scores providing the means of making the quality adjustments. Evidence on costs and QALYs will subsequently be used to inform an analysis of the cost-effectiveness of programme delivery at scale.

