#### Quantitative analysis

Descriptive statistics of survey data will be performed (frequency distribution, central tendency). Parametric and non-parametric tests will also be employed to compare the survey responses to the AIM, FIM, IAM and EQ5D before and after the SO intervention. Changes in AIM, FIM, IAM and EQ5D will be assessed using generalised linear models depending on the distribution of the outcome (continuous, binary, ordinal). All analyses will be conducted in STATA V.14.1.

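### EQ-5D and AD-SUS are scheduled only at T2 and T3, both after the workshops, so the planned before-and-after EQ-5D comparison cannot be computed as scheduled

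*Protocol article*

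**What the plan says.** The service-use, cost and quality-of-life row of Table 2 (Implementation outcomes) names "EQ5D-5L (quality of life measure) and AD-SUS (adult service receipt schedule) and semi-structured interviews and activity data" and gives T2 and T3 as its time points. The objective in that row includes "changes in quality of life associated with the implementation of the programme".

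The Outcomes section defines the time points: "T0—baseline; T1—midway through the 12-week programme (weeks 5–7); T2—immediately postperformance (12–14 weeks" for the first three, and "T3—immediately after the advocacy training for stroke ambassadors" for the last.

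Two later sections describe what will be done with the data:

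- Quantitative assessments: the researchers will "evaluate wider service utilisation and associated costs before and after participants complete the programme". Quality-of-life change, taken from EQ-5D, is listed as part of that evaluation. Utilities will then be turned into QALYs for a cost-effectiveness analysis.
- Quantitative analysis: tests will "compare the survey responses to the AIM, FIM, IAM and EQ5D before and after the SO intervention".

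The abstract also places surveys on both sides of every stage. The article schedules neither EQ-5D nor AD-SUS at T0. Demographics are the only data it mentions collecting at enrolment.

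**The concern.** A change across an intervention needs a value from before it starts. Both time points in this row fall after the workshops, which are the main exposure and the stage every enrolled survivor enters. T0 exists in the plan: Table 2 uses it for adoption, and Table 1 uses it for interviews with stroke participants. It is missing from the row whose stated purpose is change.

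Three things are at stake: the EQ-5D change across the workshops, the starting utility for any QALY calculation and, depending on recall, pre-programme service use. There is also a reporting risk. T2 to T3 would be the only change in the dataset, and it could be presented as the before-and-after result for the programme although it spans only the training stage, in those who chose it. A missed baseline cannot be collected afterwards.

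**Working it through.** **1. Schedule against planned use.**

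- EQ-5D: T2 and T3 in Table 2, so there are 0 assessments at T0. The analysis section wants values before and after the intervention. There is no before value.
- AD-SUS: T2 and T3, so again 0 assessments at T0. The assessment section wants service use and cost before and after the programme. A before value exists only if recall is long enough (step 4).
- Activity data and interviews for implementation costs: these need no survivor baseline and are not affected.

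**2. Who contributes to the one available contrast.** The Sample size section gives 75 recruits and 20% drop-out by the end of ambassador training. 75 × (1 − 0.20) = 60, which reproduces the article's figure. A T2–T3 pair needs attendance through training, so it is available for about 60 of 75. A T0–T2 pair, if T0 were collected, could be available for up to 75, and for about 60 if all the drop-out fell before T2.

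**3. How much of the period is unobserved.** Inputs: T2 at 12–14 weeks (Outcomes) and a 4-week ambassador programme (Table 2). Assumptions: T0 is at week 0 and training follows T2 directly.

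- T0–T3 = 12 + 4 = 16 weeks, up to 14 + 4 = 18 weeks.
- Share before the first EQ-5D = 12/16 = 75%, up to 14/18 = 78%.

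A gap before training would lower this share. All workshop weeks precede the first EQ-5D either way.

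**4. AD-SUS recall.** A T2 form with a recall of R weeks reaches before week 1 only if R exceeds the 12–14 weeks since the start. Even then, the form would have to separate use before week 1 from use during the workshops. The article states no recall period, so this cannot be settled from it.

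**5. What an unmeasured baseline does to QALYs.** Assume the usual trapezoid rule. With w the number of weeks from T0 to T2, and u0 and u2 the utilities at T0 and T2, the T0–T2 part is (u0 + u2)/2 × w/52. An error e in an assumed u0 therefore shifts the result by e × w/(2 × 52).

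- e = 0.05: 0.05 × 12/104 = 0.0058, up to 0.05 × 14/104 = 0.0067.
- e = 0.10: 0.10 × 12/104 = 0.0115, up to 0.10 × 14/104 = 0.0135.

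The values of e are illustrative and do not come from the article. They show that the estimate depends directly on a number the schedule does not collect.

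**The case against.** The strongest reply is that the article contradicts itself and does not describe a study deliberately run without a baseline. One table cell omits T0, while the abstract and the analysis section imply a pre-measure. The full protocol and the flowchart are not shown, and the primary-objective row of Table 1 is blank in the text available, so baseline survivor measures may be specified there. That is fair, and it is why the point is put as a conflict to resolve. It does not remove the conflict: the Table 2 row is intact and states its own time points, so if a T0 measure is intended the row is wrong.

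A second reply is that before and after completing the programme could mean T2 against T3, because the programme is described as having three stages. That reading is possible for the service-use sentence. It does not fit the EQ-5D sentence in the analysis section, which refers to the intervention as a whole, whereas T2 already lies after stage 1.

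Three stronger readings are tempting, and the documents do not support them:

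- That the whole cost objective is unanswerable. Much of it concerns the cost of implementing the programme, which comes from activity data and interviews.
- That pre-programme service use is certainly lost. This depends on the unstated AD-SUS recall.
- That the T2–T3 change measures the effect of ambassador training. The article describes no comparator arm, and the training is optional, so it is only change among those who took it.

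It is also fair to say that this is a secondary implementation objective; the primary one in Table 2 is acceptability.

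**Conclusion.** The conflict stands and is firmest for EQ-5D. With measurements at T2 and T3 only, the before-and-after EQ-5D comparison in the analysis section cannot be computed for the workshop stage, whatever the sample size. QALYs over the programme would have no measured starting utility. This follows from the schedule and the time-point definitions alone.

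For service use the same conclusion is conditional on the T2 AD-SUS recall not reaching before week 1. Implementation costing is untouched.

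The 75–78% unobserved share rests on training following T2 directly, and the QALY shifts of about 0.006 to 0.013 rest on assumed baseline errors of 0.05 to 0.10. Neither is needed for the conclusion. Adding T0 would restore an uncontrolled pre-post change. It would not by itself provide an incremental effect or a controlled cost-effectiveness estimate.

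**What to change.** In the Table 2 row for EQ-5D and AD-SUS, change the time points to T0, T2 and T3. State the AD-SUS recall period and make the T0 recall cover a period before week 1.

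In the analysis section, name T0 to T2 in all enrolled survivors as the main contrast and describe it as uncontrolled pre-post change. Start any QALY calculation from the T0 utility. Regression adjustment for baseline utility is not called for: it corrects imbalance between arms, and here there is no second arm.

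If T0 can no longer be collected, withdraw the before-after EQ-5D and QALY-change claims and report T2 to T3 only as change across the training stage.

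The same edit should reconcile the EQ-5D version, which is 5L in Table 2 and 3L in the assessment text.

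The cost is one amended table row and a pair of questionnaires at T0. The burden is small but real. The article shows a T0 interview with stroke participants but no T0 survivor questionnaire, enrolment data are collected by the arts organisation, and the advisory group asked for aphasia-friendly measures, so someone must be assigned to administer these in an accessible form.

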### Outcomes

Data on the clinical outcomes will be collected from stroke survivors who have enrolled on the SO programme (see table 1). Data on the implementation outcomes will be collected from stroke survivors who have enrolled on the SO programme as well as the wider stakeholder group involved in the SO programme, including deliverers, referrers and supporters (see table 2).

Time points for data collection: T0—baseline; T1—midway through the 12-week programme (weeks 5–7); T2—immediately postperformance (12–14 weeks); T3—immediately after the advocacy training for stroke ambassadors.

To maximise inclusivity and outcome completion, and minimise participant burden, outcome assessments, where possible, will be conducted either face-to-face, online, by telephone or via postal questionnaire depending on the outcome measures being assessed, participants’ preferences and government COVID-19 guidelines.

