Stage (2): after the performance is completed, participants will be invited to a 4-day training programme where they will learn to act as advocates for life after stroke—termed ‘stroke ambassadors’. The optional ambassador training starts with an introduction to being an ambassador and an outline of the pathways available: (a) supporting artists in hospital and community contexts, (b) speaking the press and media/advocating for life after stroke, (c) engaging in academic research and (d) joining the steering group that informs activities and directions.

The skill development training is delivered in three stages: an introduction to movement practices and the traditions of independent dance, then an introduction to voice and improvisation and, finally, an introduction to performance. Each ambassador then constructs an individually tailored programme according to their personal goals and intentions in becoming an ambassador.

The programme will take place once weekly and will be led by a team of artists and supported by a leadership coach. All training will take place on Zoom until social distancing measures are lifted, and participants are willing to meet indoors—a blended ambassador training will be offered.

Stage (3): following training, a volunteer manager will coordinate a tailored programme where ambassadors support artists in recruitment, befriend the newly discharged stroke survivors and take part in small-scale performance tours to challenge the perception of disability. The tour will be delivered online with online screenings followed by a question and answers (Q&A) session with ambassadors, taster sessions and exercises delivered online with the ambassadors.

The programme will be delivered in two cycles of the complete three-stage intervention. At the end of the two cycles of the programme, a group of newly trained ambassadors will emerge. The programme seeks to develop a national network of ambassadors who will build capacity for performance arts in healthcare and a wider capacity for healthcare. The stroke ambassadors are graduates of the 12-week workshop that receive training, based on a leadership-coaching model, and they deliver a tailored advocacy programme according to their creative skills—befriending, performance administration and support, programme advocacy.

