### Sampling

#### Sample size

We aim to recruit 75 new stroke survivors in total for the duration of the study. A prediction of 75 participants has been estimated based on the numbers that over the years running SO, *Rosetta Life* has been able to recruit in two consecutive cycles. This number has also considered the organisation being able to while maintain a manageable ratio of participants to artists and staff members, guaranteeing that SO is delivered to the highest standard.

Based on previous experience of running SO where participants then complete an ambassador training cycle, a drop-out rate of 20% is expected, and so the final number of ambassadors that complete the ambassador training is estimated to be 60.

The wider stakeholder group will be recruited from the network of people who are involved in the programme and present in the community. This includes the voluntary sector, health and social care sectors and clinical commissioners. A total of 47 stakeholders, a forecast based on the existing network numbers, will be recruited (12 carers, 10 clinical team members, 5 artists, 20 existing ambassadors).

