### Recruitment procedure

Potential stroke survivor participants will be identified through signposting in community centres and care homes as well as engaging in presentations, screenings, taster sessions and performances during the tour.

Recruitment of potential participants will be done online. Screenings of performance extracts will be followed by taster sessions online and a Q&A with ambassadors. Potential participants will be directed to the project manager at Rosetta Life who will manage all referrals.

Potential participants will be offered a Participant Information Sheet (PIS) and an Informed Consent Form (ICF) and will be explained the details of the study. Written consent will be sought following a 48 hours colling-off period.

Wider stakeholders will be recruited from the networks of people involved in the referral, delivery or support of the programme.

A recruitment log will be kept by the research team to accurately record included and excluded participants as well as missing data from dropouts to account for possible sampling bias.

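### No acceptability score is scheduled when a survivor leaves, so the survivors' primary implementation score may over-represent those who stay

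*Protocol article*

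**What the plan says.** Table 2 of the Protocol article gives the primary implementation objective as "To evaluate to what extent SO is acceptable, to survivors and wider stakeholders". The acceptability scale is scheduled at T1, T2 and T3, and the appropriateness and feasibility scales follow the same schedule. None has a T0 score. The Outcomes section defines the times as "T1—midway through the 12-week programme (weeks 5–7); T2—immediately postperformance (12–14 weeks); T3—immediately after the advocacy training for stroke ambassadors". No assessment on withdrawal is listed.

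Four other statements bear on the point:

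- **Sample size:** "We aim to recruit 75 new stroke survivors in total for the duration of the study", and then "a drop-out rate of 20% is expected, and so the final number of ambassadors that complete the ambassador training is estimated to be 60".
- **Intervention, stage 2**, which leads to T3: "The optional ambassador training starts with an introduction to being an ambassador".
- **Recruitment procedure:** a log is to record those included and excluded, and also "missing data from dropouts to account for possible sampling bias".
- **Outcomes:** "Data on the implementation outcomes will be collected from stroke survivors who have enrolled on the SO programme". Telephone and postal collection are among the permitted modes.

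Table 2 also makes adherence, drop-out counts and the reasons for dropping out an outcome in their own right. The interviews with a purposive subsample of survivors at T2 and T3 cover potential drop-out.

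**The concern.** Finding the programme hard to accept or hard to manage is one plausible reason for leaving it. If leavers are not scored, the gaps in the data are related to the quantity being measured. The first score falls at weeks 5–7, so someone who stops in the first weeks has no earlier score to carry forward or model from. T3 follows a training that survivors choose to take.

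Two readings of the results are then at risk. The level of acceptability would describe mainly those who stayed. An increase across T1, T2 and T3 could also arise partly because less satisfied people are no longer in the average. SHAPER's stated aims include scaling up and commissioning, so an optimistic survivor score would matter beyond the study.

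This concerns which data are collected. An analysis plan can say how missing scores are handled, but it cannot recover a score that nobody asked for.

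**Working it through.** **Inputs from the document.** Planned survivors: 75 (Sample size). Expected drop-out: 20%, tied to completing ambassador training (same section). Score times: T1, T2 and T3 (Table 2). The document does not give the timing of drop-out, the number lost before T1 or T2, or any difference in score between stayers and leavers.

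**Step 1: the plan's own figure.** 75 × (1 − 0.20) = 60, which matches the stated number completing the training. The remainder is 75 − 60 = 15.

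**Step 2: shift in the mean.** Let k be the number of enrolled survivors without a score and d the mean of stayers minus the mean of leavers. Then

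mean of those scored − mean of all enrolled = (k / 75) × d.

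The values of d below, in scale points, are assumptions, and so is k. The case k = 15 applies only if the 20% covers all drop-out and every leaver is unscored.

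| Unscored, k | k / 75 | d = 0 | d = 0.5 | d = 1 | d = 2 |
|---|---|---|---|---|---|
| 0 | 0 | 0 | 0 | 0 | 0 |
| 8 | 0.107 | 0 | +0.05 | +0.11 | +0.21 |
| 15 | 0.20 | 0 | +0.10 | +0.20 | +0.40 |

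The sign can reverse: if leavers scored 0.5 higher than stayers and all 15 were unscored, the shift would be 0.20 × (−0.5) = −0.10.

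**Step 3: apparent change over time.** Suppose all 75 are scored at T1, only 60 at T3, and nobody's view changes. Write m for the mean of the 60.

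- T1 mean = (60 × m + 15 × (m − d)) / 75 = m − 0.20 × d
- T3 mean = m
- Apparent rise = 0.20 × d, that is 0.20 points when d = 1

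Comparing the same people at both times would remove this rise, but the result would describe only the 60.

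**Step 4: the passages side by side.** The Outcomes section collects from enrolled survivors and allows remote modes, which makes it possible to follow people who have left. The Recruitment procedure section expects dropouts to give missing data. Nothing in the article says which governs a survivor who stopped attending before T1 or T2.

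**The case against.** The strongest reply is that the document nowhere says leavers are not approached. A reader might infer that anyone who stops before weeks 5–7 gives no score at all. That goes too far: collection is from enrolled survivors, not attenders, and a person who stops in week 3 could be sent the T1 form by post. T2 likewise carries a 12–14 week window, and the performance takes place whether or not a given survivor attends, so T2 is not closed to leavers. Only T3 clearly depends on taking part, and because the training is optional, absence at T3 need not mean dissatisfaction. All of this stands.

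It also stands that the log shows the investigators have seen the risk, that reasons for dropping out and the interviews give context, and that deliverers, supporters and referrers also rate acceptability, so the point touches the survivors' score only. An article may leave missing-data methods to a fuller document, and that silence is no fault.

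What these replies do not provide is a score from those who leave. Reasons and a purposive subsample of interviews are not AIM values, other raters cannot stand in for survivors, and permission to use the telephone is not a plan to ring people who have left.

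**Conclusion.** The point holds as a modest weakness in the collection schedule. With no score at leaving and dropouts expected to be missing, the survivors' acceptability, appropriateness and feasibility scores may over-represent those who stay and are likely to be optimistic.

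A reader might go further and conclude that the primary outcome is biased upward. The document does not support that as a fact. Direction and size depend on a stayer–leaver gap that is not reported, and drop-out for unrelated health or practical reasons would cause little bias. Nor can "a drop-out rate of 20% is expected" be read as the loss before T1 or T2, since it refers to completing ambassador training. The figure of 0.20 points per point of gap is therefore an illustration in which all 15 are unscored, and it is zero if there is no gap.

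**What to change.** 1. State that all enrolled survivors are approached for AIM, IAM and FIM at T1 and in the existing 12–14 week T2 window, whether or not they still attend.
2. Add one short AIM, IAM and FIM at leaving, by telephone or post, at the contact that already asks why the person dropped out. Include those who leave before T1.
3. Report survivor acceptability for all enrolled survivors with a score, beside the figure for those still attending, with the number unscored in each.
4. Interpret T3 as describing ambassador trainees only, and do not read a T1-to-T3 difference in means as growing acceptability among all enrolled.

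The cost is a few brief contacts, about 15 if the stated drop-out covers everyone who leaves, using modes already allowed, plus a wording change to the time points. Some leavers will not reply, so the problem is reduced but not removed, and the resulting figure may be less favourable. The change has to be made before data collection, because scores at leaving cannot be obtained afterwards.
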